### Methods in analysis to handle protocol non-adherence and any statistical methods to handle missing data {20c}

According to a treatment policy estimand strategy [37], all participants without missing outcome data will be analysed according to their randomised treatment assignment. This also applies to participants for whom one of the following post-randomisation, intercurrent events occurs which could also occur in daily clinical practice: study participants of both groups may decide for personal reasons not to take up or to withdraw from the rehabilitation programme offered. It is also possible that a change in their state of health would not allow them to undergo rehabilitation. However, it could not occur that a participant randomised to the control group switches to the intervention group, since this intervention is currently not available in clinical practice, e.g. outside the study setting.

In the main analyses, we will exclude cases with missing data on the variables considered in the analysis of the primary and secondary outcomes due to dropout or loss to follow-up. If available, we will report the reasons for missingness. We will provide a table showing the distribution of baseline characteristics stratified by intervention group for all participants being randomised and for all participants being analysed. We will impute the missing values using multiple imputation and provide sensitivity analyses for primary and secondary outcomes using the imputed data [38].

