### Objectives {7}

The overall objective is to assess the effectiveness of the developed platform-based case management approach (intervention condition) for rehabilitation care planning compared to treatment/care planning as usual (control condition).

The primary estimand is defined by the following attributes:Treatment condition: assignment to platform-based case management approach (intervention condition) for rehabilitation care planning compared to treatment/care planning as usual (control condition) including the effects of withdrawal from rehabilitation care.Target population: adults aged 40 to 60 years with a minimum of 4-week (20 workdays) work disability due to musculoskeletal, oncologic or psychological conditions or the post-COVID-19 syndrome (PCS) within the last 6 months prior to study inclusion (patient-reported information) and a high risk of early retirementEndpoint: cumulative sick leave days, health insurance data, during the period of 12 months after completion of the treatment (t1 to t2).Intercurrent events and strategies to address them: plausible and important intercurrent events include the patients’ withdrawal from the rehabilitation due to any reason, are addressed in the treatment condition attribute and handled with the treatment policy strategy.

The secondary estimands differ from the primary only in regard to the endpoints: self-reported cumulative sick leave days during the period of 12 months after completion of the treatment (t1 to t2); work ability, as measured by the Work Ability Index (WAI, German version) [20] and the health-related quality of life, as measured by the Short Form 36 Health Survey (SF-36, German version) [21, 22] 12 months after completion of the treatment (t2).

We also aim to describe the delivered process in terms of adherence, use of treatments (MT/NMSM), implementation of the intervention, treatments (MT/NMSM) recommended on the digital platform as well as involvement of a social worker. Moreover, facilitating and hindering factors that influence the success of the intervention and to identify adaptations that are necessary for a successful implementation will be investigated qualitatively as a part of the process evaluation.

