### Criteria for discontinuing or modifying allocated interventions {11b}

PCPs as well as patients will be able to withdrawal consent for study participation (e.g. in case of deterioration of health condition) at any time without giving reasons or experiencing any disadvantages. Modifying allocated interventions is not applicable as care planning is meant to be flexible.

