#### Primary outcome

Number of days of sick leave: postal enquiry health insurance (time periods inquired: 6 months before baseline till t0, t0 till t1, t1 till t2). Patients will receive a prepared form and a stamped envelope so that the request can be sent to their health insurance directly after signature. The aggregation method for both groups will be the mean number of sick days between t1 and t2 assessed at t2.

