### Sample size {14}

Based on a systematic review of workplace interventions to prevent work incapacity [27], a difference of 34 days of incapacity to work (12-month period between t1 (assumed end of treatments) and t2) between the intervention and control group is assumed and applied for sample size calculation. A sample size of 149 patients in each group will have 90% power to detect a difference in means of 34 days of sick leave assuming that the common standard deviation is 90 days using a two-group *t*-test with a 5% two-sided significance level. Assuming that about 15% will be lost to follow-up or withdraw from the study, 352 participants have to be included. If a PCP would recruit six participants, about 59 PCPs must participate in the study. Sample size calculation was performed using R: A Language and Environment for Statistical Computing [28] and the package pwr [29]. The number of patients to be recruited per practice (*n* = 6) is based on feasibility and experience regarding the reasonableness for participating practices.

Participating in the interview study, as a part of the process evaluation, will be optional. The sample size for interviews will depend on data saturation [30]. We plan on interviewing 12 to 25 PCPs and patients each. Persons involved in the CC (public health physician, case administrator, social worker) will also be invited for the interview.

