## Statistical methods

### Statistical methods for primary and secondary outcomes {20a}

The participant flow will be reported according to the CONSORT guideline [23], which will show withdrawals and drop-outs. PCP and patient characteristics as well as outcomes, and process evaluation data will be descriptively reported using mean values and standard deviations for normally distributed data and median and range for not normally distributed data. Categorical data will be presented in amount and percentage.

All analyses will be performed using a modified intention-to-treat approach on both primary and secondary outcomes. According to a treatment policy estimand strategy, all participants without missing outcome data will be analysed according to their randomised treatment assignment. However, we will exclude cases with missing data due to dropout or loss to follow-up from the main analyses (for details, see item 20c).

For the primary outcome, we will fit a linear regression model with the cumulative sum of sick leave days during the period between t1 and t2, reported by health insurance, as a dependent variable and the treatment indicator as an independent variable, adjusted for sex, age, baseline number of sick leave days and baseline WAI [20] to control for differences between groups at baseline despite randomisation. Additionally, PCP IDs will be included as random intercepts in order to adjust for influence from stratified randomisation [35]. We will report the primary outcome as adjusted between-group mean differences with a 95% confidence interval. We will conduct analogue analyses for the secondary outcomes of self-reported sick leave days, work ability (WAI, 20) and health-related quality of life (SF36, 21, 22).

Interview data will be transcribed and qualitatively analysed using thematic analysis [36].

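### The main analysis is complete-case, with an inconsistent inclusion rule and an unstated missing-data assumption, while the better-suited multiple imputation is only a sensitivity analysis

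*Protocol article*

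**What the plan says.** The relevant statements are spread over several sections of the protocol article.

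- **Objectives {7}.** The primary estimand is the effect of assignment on insurer-recorded sick leave days from t1 to t2. Withdrawal from rehabilitation is "handled with the treatment policy strategy".
- **Statistical methods {20a}.** The approach is called modified intention-to-treat, and "all participants without missing outcome data will be analysed according to their randomised treatment assignment". The next sentence excludes patients with data missing through dropout or loss to follow-up and refers to {20c}. The model adjusts for sex, age, baseline sick leave days and baseline WAI, with a random intercept for the physician.
- **Missing data {20c}.** The first paragraph repeats the rule based on the outcome. The second says: "In the main analyses, we will exclude cases with missing data on the variables considered in the analysis of the primary and secondary outcomes", again for dropout or loss to follow-up. Multiple imputation is planned for sensitivity analyses only. Reasons for missingness and a table of randomised versus analysed patients are also planned.
- **Discontinuation {11b}.** Patients may "withdrawal consent for study participation (e.g. in case of deterioration of health condition) at any time".
- **Primary outcome.** The insurer data depend on a form that the patient signs: "Patients will receive a prepared form and a stamped envelope so that the request can be sent to their health insurance directly". Insurer days are also requested for t0 to t1.

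**The concern.** There are two problems.

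**The inclusion rule is inconsistent.** One sentence keeps everyone with an observed outcome. The other excludes on any variable in the analysis, which includes the baseline covariates. The dropout qualifier does not settle this, because baseline assessment comes before randomisation and a missing baseline value is hardly the result of dropout. Nor does it cover a patient who stays in the study but whose insurer does not answer.

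**The headline estimate rests on an assumption that is not written down.** Complete-case regression is in general unbiased only if, given treatment and the model covariates, missingness is unrelated to the outcome. Health that worsens after baseline is not among those covariates, yet the plan gives it as an example of why a patient might leave. Patients know their arm, and the outcome request needs their signature, so the reasons for loss could differ by arm. The t0-t1 sick leave data, which could carry information about this, do not enter the main model.

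At stake is some bias in the adjusted mean difference and the avoidable loss of patients whose outcome is known.

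**Working it through.** **1. The plan's own figure.** Sample size {14} states: "149 patients in each group will have 90% power to detect a difference in means of 34 days of sick leave". Its other inputs are an SD of 90 days in both arms, a two-sided alpha of 5% and 15% loss.
- Standardised difference: 34/90 = 0.378.
- Two-sample t-test (noncentral t): n = 148.2, so 149 per arm; power at 149 is 90.2%.
- Inflation for loss: 149/0.85 = 175.3, so 176 per arm and 352 in total.

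The stated figures reproduce. The sample size is not at fault, and it already allows for excluding 15%.

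**2. Power under further exclusion.** Analysed per arm = 352 × (1 − m)/2, same t-test. Values of m above 15% are assumptions.
- m = 0: 176.0 per arm, 94.2% (a ceiling, since imputation does not recover all lost information)
- m = 15%: 149.6 per arm, 90.3%
- m = 20%: 140.8 per arm, 88.5%
- m = 25%: 132.0 per arm, 86.4%
- m = 30%: 123.2 per arm, 84.0%

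**3. The two rules applied to three patients.**
- *Stops rehabilitation, insurer data obtained, covariates complete:* analysed under both rules, as treatment policy requires.
- *Insurer data obtained, baseline WAI missing:* analysed under the outcome rule. Excluded under the any-variable rule, unless the dropout qualifier is read as sparing baseline gaps. The two sentences do not give one answer.
- *Still in the study, insurer does not reply:* not promised analysis by the outcome rule, and not described by an exclusion limited to dropout and loss to follow-up. No rule applies.

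**4. Bias by simple arithmetic (rates and differences assumed).**
- Loss differs by arm: bias = (loss in intervention − loss in control) × excess sick days among the lost. With 20% versus 10%: 0.10 × 45 = 4.5 days and 0.10 × 90 = 9.0 days, or 13% and 26% of 34. This is before covariate adjustment. It favours the intervention, and swapping the rates reverses the sign.
- 15% lost in each arm, but the treatment difference among the lost departs from that among the observed by D: bias = 0.15 × D. For D = 10, 34, 45 and 90 days this is 1.5, 5.1, 6.8 and 13.5 days.

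**5. Bias with a baseline covariate in the model (simulation, all settings assumed).** 1,000,000 patients, effect −34 days, outcome SD about 90, 15% missing overall, coefficient of t0-t1 sick leave on the outcome (standardised) 0.3 to 0.7. Complete-case estimate minus full-data estimate:
- missingness depends only on the model covariate: below 0.1 day
- depends on t0-t1 sick leave equally in both arms: 0.4 to 0.8 days, towards no effect
- depends on it in the intervention arm only: 2.8 to 6.7 days, exaggerating benefit
- depends on it in opposite directions by arm: 5.5 to 12.9 days, exaggerating benefit (an extreme case)

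In the last three settings an imputation model that includes t0-t1 data could address the bias. The complete-case model does not use those data.

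**The case against.** The strongest defence is that the plan is more coherent than it first appears, and much of it stands.

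- **Treatment policy.** A reader might infer that a complete-case analysis contradicts this strategy. It does not. The strategy concerns intercurrent events, and {20c} keeps patients who decline, stop or cannot undergo rehabilitation if their outcome is observed. Leaving the study is a missing-data matter, and the withdrawal text in {11b} is about consent to the study.
- **Modified intention-to-treat.** A reader might also infer that dropping missing outcomes breaks the plan's own analysis set. It does not, because {20a} defines the set that way. Only the covariate wording conflicts.
- **Dropping anyone with a gap.** The dropout qualifier forbids reading the rule so broadly. Nor does the article say whether the baseline sick leave covariate comes from the insurer or from self-report.
- **Size and direction.** Nothing in the document shows that loss will differ by arm or in which direction, and the retention measures apply to both groups. One example of a reason for withdrawal does not establish it.
- **Imputation is no cure.** Standard multiple imputation also assumes missingness at random. Self-reported t1-t2 days are collected at t2, so patients lost earlier lack them too.
- **Existing safeguards.** Imputation, reasons for missingness and a randomised-versus-analysed table are already planned.

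What remains is the contradiction on covariates, the gap for unanswered enquiries, and a headline estimate that ignores collected data under an unstated assumption. A sensitivity analysis shows the problem but does not change which estimate is reported as the result.

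**Conclusion.** The point holds as a should-fix. The inclusion rule needs one consistent statement, and complete-case analysis is the weaker choice for the primary result given what the trial collects.

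The likely size is modest. Under assumed arm-differential dropout the bias is about 3 to 9 of the 34 target days. Only the extreme opposite-direction setting, or a very different effect among the lost, goes beyond that. With one mechanism in both arms it is under 1 day. These figures rest on assumed loss rates, excess days and correlations, so they show what is possible and do not predict bias in favour of the intervention.

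Power is a minor matter: 88.5% at 20% total exclusion against 90.3% at the planned 15%. Trial status reports that recruitment ended early for low numbers, so counts built on 352 no longer describe this trial. The bias does not depend on that number, but a smaller sample makes it harder to justify discarding observed outcomes.

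**What to change.** 1. State one analysis-set rule in {20a} and {20c}: every patient with an observed primary outcome is analysed as randomised, and missing baseline covariates are imputed. Say how an unanswered insurer enquiry is treated, and which source supplies baseline sick leave days.
2. Make the planned multiple imputation the primary analysis, in all randomised patients, by arm, under a stated missing-at-random assumption. Include t0-t1 insurer days, t1 WAI and SF-36, and self-reported days where available. These auxiliaries matter: where only the outcome is missing, imputing from the model's own variables adds essentially nothing to complete-case analysis.
3. Keep the complete-case model as a sensitivity analysis.
4. Add a sensitivity analysis for departures from missing at random, for example by shifting imputed sick leave days by arm over a stated range, because imputation alone does not cure outcome-dependent dropout.

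Decide this while the statistician is still blinded and before the analysis plan is finalised, as {17a} allows.

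The cost is mainly wording and a little more analysis work, since the imputation is already planned. If the change counts as a protocol change, {25} requires approval from the funder and the Ethics Committee. The price is reliance on the imputation model, which helps least for patients lost before t1.

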### Plans to give access to the full protocol, participant-level data and statistical code {31c}

The full protocol and the resulting data set (individual participant data for the principle analysis) will be made available to other researchers upon reasonable request.

## Oversight and monitoring

### Composition of the coordinating centre and trial steering committee {5d}

The direct study team will consist of the scientific staff and study assistants. The study team will run the trial day-to-day and provide organisational support. The study team will meet at least on a weekly basis. The trial statistician will not be a member of the study team. The trial steering committee will consist of the members of the study team, the chief investigator, the overall study coordinators, the case administrator, public health physician and social worker. Meetings will take place every second week to monitor the conduct and progress of the study.

### Composition of the data monitoring committee, its role and reporting structure {21a}

A data monitoring committee will not be established. However, data monitoring will be carried out by the scientific staff of the study team and the case manager will monitor adherence to the protocol in the CCs. If there is any uncertainty, issues will be discussed in the weekly study team meetings and if necessary in the biweekly meetings of the trial steering committee.

### Adverse event reporting and harms {22}

The intervention (CC) is not expected to lead to adverse events or harms. If significant adverse events occur due to the digital case management, the intervention will be stopped. Participants will not be asked specifically about potential harms. There will be an opportunity for participants in the interview study to report on potential harms through observations and experiences.

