### Trial design {8}

The RehaPro SERVE Trial is an investigator-initiated, pragmatic, multicentre, randomised and controlled two-arm parallel-group superiority trial. Initially, PCPs will be recruited by the study team, enrolled in the study and tasked with recruiting patients with musculoskeletal, oncological or psychological conditions or PCS. Patients will be randomised using a 1:1 allocation to either the intervention group (rehabilitation care planning with a multidisciplinary platform-based case management approach) or the control group (treatment as usual) stratified by primary care practice and using permuted blocks. A parallel process evaluation will be completed, which will examine adherence, treatment decisions (MT/NMSM), implementation of the intervention, as well as involvement of the social worker. An interview study will be part of the process evaluation and will be conducted with PCPs, patients and other stakeholders involved in the intervention (public health physician, case administrator and social worker), to qualitatively investigate facilitating and hindering factors which influence the success of the intervention and to identify adaptations that are necessary for successful implementation. Reporting of the study will follow the CONSORT guidelines for reporting parallel group randomised trials [23].

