### Strategies to improve adherence to interventions {11c}

The case manager will monitor adherence for PCPs in the CC. In the event of difficulties (e.g. delayed processing, missing information on the platform), the study team will be informed and contact the PCP to provide flexible support if required. The case manager also monitors the completeness of the additional questionnaires from patients in the intervention group (see SPIRIT item 18a) on the platform. The social worker can assist patients from the intervention group with all organisational issues regarding the intervention. As part of the monitoring and control process, meetings with the trial steering committee will be held every 14 days to discuss deviations and violations of the protocol and to assess the risk of such (composition of the trial steering committee is explained in SPIRIT item 5d). Adherence to resulting treatment decisions (MT/NMSM) will not be monitored, as the focus of the trial lies on the procedures of the CC. However, if needed, the social worker can be administered to support patients in taking up the offer.

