**Table 1 Tab1:**
[figure not shown]
Time schedule of patients’ enrolment, interventions and assessments

*HADS* Hospital anxiety and depression scale, *WAI* Work ability index, *SF-36* Short Form 36 Health Survey, *MT* Medical treatment, *NMSM* Non-medical support measures

Interviews with PCPs will start earliest after closure of the CC of their first patient allocated to the intervention group and are planned to be conducted at various time points in order to provide a broad picture. Interviews with patients will also take place at different time points, but no earlier than after the offer of treatment (MT/NMSM). Other persons involved in the CC (public health physician, case administrator and social worker) will be asked for an interview at the end of the RCT.

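### The plan would stop the intervention for adverse events but does not ask participants about harms, and it collects no adverse events in the same way in both arms (minor)

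*Protocol article*

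**What the plan says.** The section on adverse event reporting and harms {22} first gives its reason: the case conference is not expected to cause harm. It then states: "If significant adverse events occur due to the digital case management, the intervention will be stopped. Participants will not be asked specifically about potential harms". The one participant route it names is the interview study: "There will be an opportunity for participants in the interview study to report on potential harms through observations and experiences".

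Interviews are optional, and Sample size {14} gives their number: "We plan on interviewing 12 to 25 PCPs and patients each". Under Participant timeline {13}, patient interviews come only after a treatment offer, and for physicians: "Interviews with PCPs will start earliest after closure of the CC of their first patient allocated to the intervention group".

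Fortnightly steering meetings are held "to discuss deviations and violations of the protocol and to assess the risk of such" (section {11c}). The section on the steering committee {5d} puts their purpose this way: "Meetings will take place every second week to monitor the conduct and progress of the study". The case administrator, public health physician and social worker are members. Section {21a} provides no data monitoring committee and sends uncertainties found in monitoring to the weekly team meeting and, if needed, to the steering committee.

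**The concern.** A commitment to stop needs information that could trigger it. Here the commitment and the decision not to ask for that information stand in adjacent sentences. Because the decision is stated, it is not a detail that the article has left to the full protocol.

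Two things are at stake. First, a harm that only the patient perceives, and does not raise with anyone, may not reach those who would decide on stopping. Second, at the end of the trial nobody can set unwanted events in one arm against those in the other. The commitment covers only events caused by the case management. Patients and staff are unblinded (section {17a}), so that causal judgement would be made without blinding and without a control-arm count beside it.

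**Working it through.** **1. What is recorded that bears on harm**

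- *Outcomes {12}:* sick leave from insurers, self-reported sick leave, WAI and SF-36, in both arms.
- *Data collection {18a}:* HADS-D at baseline, 6 and 18 months (t0, t1, t2), in both arms.
- *Process evaluation:* withdrawals with reasons, and treatments used with start and end dates by patient questionnaire at t1 and t2. Neither item is restricted to one arm, whereas other items in that list are marked as intervention group only.
- *Section {11b}:* a patient may withdraw without giving a reason, so withdrawal reasons will be incomplete.
- *Adverse events:* no such variable appears in any of these lists.

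**2. Passive routes**

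- Every intervention patient's PCP takes part in the conference and discusses its proposal with the patient (section {11a}).
- The case administrator is in every conference and on the steering committee (sections {11a}, {5d}).
- Every patient in both arms has t1 and t2 contacts with a research assistant (sections {13}, {18a}, {18b}).

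An event can surface through any of these, but only if someone mentions it. The PCP and t1/t2 routes exist in both arms; the conference route exists only in the intervention arm.

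**3. Planned numbers**

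The protocol's own figures hold together: 149/0.85 = 175.3, rounded up to 176 per arm, and 2 × 176 = 352.

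**4. Reach of the interviews** (taking every patient interview to be in the intervention arm, the most favourable case)

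- Patients: 12/176 = 6.8% and 25/176 = 14.2%.
- PCPs: six patients per practice at 1:1 gives three intervention patients each, so 12 × 3 = 36 (20.5%) to 25 × 3 = 75 (42.6%). This is an upper bound, because a PCP may be interviewed after the first conference only.

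**5. What silence in the patient interviews would show**

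With no harm mentioned by n patients, the one-sided 95% upper limit for the harm rate is 1 − 0.05^(1/n). If only half of those affected would mention it, the limit doubles.

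| Patients asked | Full disclosure | Half disclose (assumed) |
|---|---|---|
| 12 interviews | 22.1% | 44.2% |
| 25 interviews | 11.3% | 22.6% |
| 50 per arm (assumed) | 5.8% | 11.6% |
| 100 per arm (assumed) | 3.0% | 5.9% |
| 149 per arm (planned at follow-up) | 2.0% | 4.0% |

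The rows for 50 and 100 are there because recruitment closed early and the number reached is not given. All rows assume representative respondents. They describe the patient-report route alone and do not measure how reliably the stopping commitment would work.

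**6. Timing** (Trial status; Participant timeline {13})

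- Enrolment ran from September 2022 to December 2023, 16 calendar months.
- t1 falls from about March 2023 to June 2024, and t2 from about March 2024 to June 2025.
- Patients enrolled by June 2023 (the first 10 months) reached t1 before recruitment closed. Had they been asked, their answers could have informed conferences still running for later patients.
- A patient's own conference is expected to be over by t1.

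**The case against.** The strongest reply is that this is a disclosed and reasoned choice. The intervention is a way of planning care, harm is not expected, and a promise to stop does not logically require solicited reporting. The passive routes are also wider than the interviews: a PCP and a case administrator are involved in every conference, and staff see or telephone every patient twice more. The interviews are sized for saturation and were never meant to estimate a rate. The full protocol may also hold a procedure for events that staff hear of unprompted.

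Much of this stands. It keeps the point minor and makes the limits in the table an illustration only. It does not remove the point, because none of these routes asks both arms the same question, and the protocol itself treats harm as possible by providing for stopping.

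A reader might also go too far in the other direction, in three ways:

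- *That the stopping commitment is empty, or that harm would go unseen.* The passive routes above contradict that.
- *That treatment uptake is unrecorded*, from "Adherence to resulting treatment decisions (MT/NMSM) will not be monitored, as the focus of the trial lies on the procedures of the CC". That sentence concerns monitoring of adherence; treatments used are asked about at t1 and t2.
- *That the missing link between platform data and research data prevents a comparison by arm.* It does not: such a comparison needs only the allocation, which the randomisation database holds.

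**Conclusion.** The point holds as a minor design weakness, mainly one of harms reporting. The trial will be able to compare deterioration on its outcome scales by arm. It will not be able to compare unwanted events, and an event judged to be caused by the case management will have no control comparison. If no harm is mentioned in the patient interviews, that alone leaves a harm rate of up to 22% or 11% open, under the assumptions stated with the table.

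The documents do not show that harm is likely. Nor do they say whether stopping would apply to one patient or to the whole trial; if to one patient, asking at t1 would add nothing for that patient, whose conference should be over by then. The primary analysis and the sample size are unaffected.

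**What to change.** Add one open question on unwanted events, with date and perceived relation to care planning, to the t1 and t2 assessments. Use the same wording in both arms. Review the answers at the existing fortnightly steering meetings while conferences are still running, and report counts by arm.

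The cost is one question at contacts already planned, an amendment that needs funder and ethics approval (section {25}), and some reports unrelated to the intervention. For stopping, the gain is limited to later patients. With recruitment closed in December 2023, a late addition serves mainly the report.

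If follow-up is complete, the remedy is a statement in the results paper that harms were not systematically collected, with no claim that the intervention was harmless.
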